**3. AIMS/OBJECTIVES/HYPOTHESES**

*Aim*

To compare the treatment efficacy of anorectal biofeedback (clinical indicators and physiological parameters) performed with a novel home-based device with conventional therapy options in patients with functional defecation disorders.

*Faecal incontinence is a heterogeneous condition, there is no single parameter to adequately define or represent an optimal way of assessing clinical outcomes. A range of subjective and physiological measures of bowel function are used as outcomes measures.*

*Site 1 Specific* - A feasibility assessment at Site 1 will evaluate the accuracy and repeatability of the prototype (V2) against anorectal manometry*

1. *Evaluate the capability of experimental device to generate anorectal exercise profiles*
2. *Compare the accuracy of experimental device against anorectal manometry*

*Site 1 and Site 2*

*Subjective primary outcome measures*

1. *Vaizey and Wexner faecal incontinence scores*
2. *Faecal incontinent episodes (days per week)*

*Objective primary outcome measure*

1. *Anal sphincter squeeze pressure (mmHg)*

*Secondary outcome measures*

1. *Anal sphincter resting pressure (mmHg)*
2. *Patient’s own view of effectiveness rating (“worse”, “same”, “improved”, or “cured”) and rating of that change in an ordinal scale of – 5 to + 5*
3. *Frequency of bowel motions and symptoms*
4. *[Experimental device group] Usability interview – 1. Ease of use, 2. Clarity of instructions, 3. Ease of cleaning, 4. Any additional Issues*

Hypotheses

We hypothesised that instrumented home BF therapy with the novel device is as efficacious as clinic-based BF therapy

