**5.3 Data source and Population**

*Study population and size*

The Site 1 feasibility study will be a pilot study involving n=15 (n=20 with 33% dropout) participants per group. This study will evaluate the capability of the experimental device to provide instrumented BF (create distinct BF exercise profiles and is understood by the user) and compare the data against anorectal manometry. This is similar to our previous study [18] but will use the new prototype (V2) and be in a patient population.

The data from this site will not be analysed together with data from Site 2, given the differences in methodology. However, data from Site 1 will be used to improve the statistical analysis plan for Site 2. Currently, the power calculations for Site 2 are based on a previous study [19], but data from Site 1 will be integrated to improve the calculation of sample size and power for Site 2.

Site 2 sample size and power calculations

Based on a previous study of biofeedback treatment for faecal incontinence [19], we estimate that for assessing home-BF and clinic-BF efficacy with a sample size of 30 per group (n=40 with 33% dropout), the paired t-test at the 0.05 significance level can detect a mean change in anorectal function measure of at least 0.45 SD with 0.80 power. This corresponds to at least a mean decrease of 8 in Vaizey/Wexner faecal incontinence score, decrease of 0.6 in faecal incontinence episodes, and 40% increase in anal sphincter squeeze pressure.

For the non-inferiority study, based on changes in the primary outcome measures, with n=30 per study arm, the test for non-inferiority has 0.70 power to reject, at the 0.05 significance level, the null hypothesis that the mean change due to home-BF is smaller than clinic-BF by at least 0.44 SD in favour of he alternative hypothesis that mean changes due to home-BF is no more than 0.44 SD lower than clinic-BF (i.e. Ho: ΔHB-ΔOB<−0.44SD vs. Ha: ΔHB-ΔOB≤−0.44SD).

Using estimates from previous study [19], we consider home-BF no worse than or better than clinic-BF if the home-BF group had at least 9 point decrease in Vaizey/Wexner faecal incontinence score (11 for clinic-BF, SD=3), 0.95 days/week decrease in faecal incontinence episodes (1.1 for clinic-BF, SD=0.25), and 19 mmHg increase in anal sphincter squeeze pressure (25 mmHg for clinic-BF, SD=10).

*Data collection/Outcome measurements*

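### Site 2 non-inferiority: 30 per arm and a 0.44 SD margin give power of about 0.52, not the stated 0.70, and the raw thresholds that follow imply wider margins

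*Protocol*

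**What the plan says.** Section 5.3 of the Protocol, under the Site 2 sample size and power calculations, plans a "sample size of 30 per group (n=40 with 33% dropout" in brackets. It then gives the power for non-inferiority: "with n=30 per study arm, the test for non-inferiority has 0.70 power to reject, at the 0.05 significance level". The null hypothesis to be rejected is that home treatment falls short of clinic treatment by 0.44 SD or more, and the comparison is on change scores ("based on changes in the primary outcome measures"). The hypotheses are printed as "Ho: ΔHB-ΔOB<−0.44SD vs. Ha: ΔHB-ΔOB≤−0.44SD". Both inequalities point the same way, so I take the direction from the sentence in words.

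The section gives no sidedness for the 0.05, no true difference under the alternative and no covariate adjustment.

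The next paragraph sets out in raw units when home biofeedback counts as no worse than clinic biofeedback:

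- **Incontinence score:** a fall of 9 points, against 11 in clinic (SD 3).
- **Incontinence episodes:** a fall of 0.95 days/week, against 1.1 (SD 0.25).
- **Squeeze pressure:** a rise of 19 mmHg, against 25 (SD 10).

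The three are joined by the word *and*. Section 3 lists these measures as primary outcomes, with "Vaizey and Wexner faecal incontinence scores" as one entry. Section 5.3 also says that the Site 2 calculation will be improved with Site 1 data.

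**The concern.** Non-inferiority is the trial's main hypothesis, and the 0.70 is the only power given for it. A 0.44 SD margin with 30 per arm looks too narrow for that figure. If 0.44 SD is the margin meant, a device that truly matches clinic treatment has about an even chance of being shown non-inferior on any one outcome, while the protocol tells its readers 70%.

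The paragraph that follows adds a second problem. Read as margins, its thresholds are wider than 0.44 SD, so the plan holds two margins for one test. The power cannot be stated correctly until one of them is chosen. The figure is also for a single outcome, whereas three thresholds are listed together.

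**Working it through.** **Inputs from the Protocol**

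- 30 evaluable per arm, 40 randomised per arm, 33% dropout, significance level 0.05, margin 0.44 SD, stated power 0.70 (Section 5.3).
- Parallel groups, 1:1 allocation (Section 5.8).

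**Assumptions, because the Protocol is silent**

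- The 0.05 is one-sided, which is the more favourable reading; 0.025 is also shown.
- True difference zero, in line with the Section 3 hypothesis of equal efficacy.
- Unadjusted two-sample t-test on change scores.

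**Step 1. Attempt to reproduce 0.70**

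Power = P(T > t_crit), where T is noncentral t with 2n − 2 degrees of freedom and noncentrality margin × √(n/2).

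For n = 30 and margin 0.44: df = 58, noncentrality = 0.44 × √15 = 1.704, critical value 1.672, power 0.516. The normal approximation gives Φ(1.704 − 1.645) = 0.524. The stated 0.70 is not reproduced.

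**Step 2. Other readings at 0.44 SD (t-based)**

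| Reading | Power |
|---|---|
| 30 per arm, one-sided 0.05 | 0.52 |
| 27 per arm (40 × 0.67 = 26.8), one-sided 0.05 | 0.48 |
| 40 per arm (no dropout), one-sided 0.05 | 0.62 |
| 30 per arm, one-sided 0.025 | 0.39 |
| 30 per arm, one-sided 0.10 | 0.66 |
| Paired formula, n = 30, one-sided 0.05 (wrong design for two arms) | 0.76 |

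None gives 0.70. At one-sided 0.05, reaching 0.70 takes 50 evaluable per arm at 0.44 SD (49 gives 0.698), or a margin of 0.567 SD with 30 per arm (0.598 SD with 27).

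**Step 3. Margins implied by the raw thresholds**

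- Score: (11 − 9)/3 = 2/3 = 0.67 SD
- Episodes: (1.1 − 0.95)/0.25 = 0.15/0.25 = 0.60 SD
- Squeeze pressure: (25 − 19)/10 = 6/10 = 0.60 SD

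Per-outcome power, one-sided 0.05, true difference zero:

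| Margin | n = 30 | n = 27 |
|---|---|---|
| 0.44 SD | 0.52 | 0.48 |
| 0.60 SD | 0.74 | 0.70 |
| 0.67 SD | 0.82 | 0.78 |

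**Step 4. Joint power, only if all three outcomes must pass**

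Simulated with n = 30, one-sided 0.05, true differences zero and equal correlation between outcomes. The correlations are assumed.

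| Correlation | Raw thresholds (0.67, 0.60, 0.60 SD) | 0.44 SD on all three |
|---|---|---|
| 0 | 0.45 | 0.14 |
| 0.5 | 0.56 | 0.26 |
| 0.8 | 0.64 | 0.36 |

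Check at correlation 0: 0.818 × 0.743 × 0.743 = 0.45, and 0.516³ = 0.14.

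**The case against.** The strongest objection is that 0.44, not 0.70, may be the wrong entry. At the 0.60 SD implied by two of the raw thresholds, power is 0.74 with 30 per arm and 0.70 with 27, which is close to or equal to the stated figure. This stands. A reader might infer from Step 1 that the trial's power simply is 0.52. The document does not support that, because it contains two sets of margins and does not say which governs.

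Unstated assumptions could also lift the figure. By the normal approximation, a true advantage for the home device of about 0.12 SD would give 0.70 at 0.44 SD: (1.645 + 0.524)/√15 − 0.44 = 0.12. So would adjustment for a baseline covariate correlated at about 0.62 with the outcome. The Protocol mentions neither, and its data-analyses text in Section 5.8 names only paired t or Wilcoxon tests and chi-square tests. This part of the objection limits how firmly 0.52 can be put forward, but does not explain the 0.70.

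A reader might take the *and* in the threshold paragraph as an all-must-pass rule and quote 0.14 to 0.36 as the trial's real power. No such rule is written. The paired-test paragraph uses the same kind of list, apparently outcome by outcome. Those low values also combine the conjunction from one paragraph with the margin from another; the thresholds that the word actually joins give 0.45 to 0.64.

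Section 5.8 says the null will be accepted or rejected, from which one might infer that a miss would be reported as inferiority. Nothing in the Protocol says how a failed test would be reported, so I do not rely on it.

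Finally, the trial is labelled a pilot and the Site 2 calculation is to be updated with Site 1 data. That makes the update a natural place to apply the correction. It does not make the present figure right, and an update by the same method could repeat the error.

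**Conclusion.** The point holds as an inconsistency between power, sample size and margin. On the figures in the power sentence, power is 0.52 rather than 0.70, a gap of about 18 percentage points. It is 0.48 with 27 per arm, and 0.39 with 30 per arm at one-sided 0.025. This rests on one-sided alpha 0.05 (except where shown), a true difference of zero and an unadjusted comparison.

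The mismatch is certain under these ordinary assumptions; the replacement value is not. It is 0.52 if 0.44 SD is the margin, and 0.74 to 0.82 per outcome (0.70 to 0.78 with 27) if the raw thresholds are. Joint power matters only if all three outcomes are required, and the Protocol does not say that they are.

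**What to change.** In Section 5.3:

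1. Reconcile the margin so that the hypotheses and the raw thresholds agree, and correct the direction of the printed inequalities.
2. Restate the power for that margin with its assumptions: one-sided alpha 0.05, true difference zero, unadjusted comparison, and the evaluable number per arm. If 0.44 SD is kept, the figure is 0.52 with 30 or 0.48 with 27. If the raw thresholds are kept, it is 0.74 to 0.82 with 30 or 0.70 to 0.78 with 27.
3. Say that the figure is per outcome.
4. Say whether all three outcomes must pass. If so, give the joint power for the chosen margins, with the assumed correlations: about 0.45 to 0.64 for the raw thresholds, or 0.14 to 0.36 at 0.44 SD, both with 30 per arm.
5. Use the same corrected method when Site 1 data update the calculation.

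This is a change of wording and needs no change in enrolment. The cost is that the stated power may become less favourable. Rewording does not raise the power itself: keeping 0.44 SD and wanting 0.70 on one outcome would take 50 evaluable per arm, which is a separate decision for the sponsor.

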**5.8 Study Procedure**

Patients arrive at a study site to undergo routine diagnostic anorectal manometry. If a patient is diagnosed with a functional faecal incontinence and suitable for BF therapy they will be asked to take part in this study. Randomization used permuted blocks of 4 with 1:1 assignment into the parallel study groups described in Section 5.3. Random numbers generated in advance and placed into sequentially numbered opaque envelopes, sealed and used for subject assignment. After screening, and once patients met the study inclusion and exclusion criteria, patients are enrolled into one of the treatment arms, by opening the sealed envelope. The therapist ([name] or [name]) and patient are not blinded to the treatment.

The specialist nurse therapist provides advice regarding bowel habits, exercise, laxatives, dietary fibre and fluid intake, and timed-toilet training during the initial consultation to all participants. The therapist will teach participants how to improve their push effort by using postural and diaphragmatic breathing techniques and instruct them to practice these manoeuvres at home for 15 minutes, three times a day.

*Clinic-based biofeedback using anorectal manometry*

In addition to the aforementioned general instructions, participants receiving clinic-based BF (**Group A**) will be attending a maximum of six in-clinic therapy sessions over 2 months. BF training uses the anorectal manometry. Manometry catheters have several circumferential pressure sensors that straddle the entire anal canal and a proximal sensor placed in the rectum, providing continuous and dynamic spatiotemporal mapping of anorectal pressures. During anorectal BF therapy, a sheath is placed over the catheter and inserted into the anal canal. The system and therapist provides provide visual/audio feedback to the patient and record exercise parameters to establish baseline or evaluate progress. The key BF manoeuvres are:

1. **Rest:** after probe placement, a period of time is given for the patient to relax such that anal sphincter tone returns to basal levels. Anal resting pressure is measured using the averaged resting pressure over the length of the anal canal over a period of 20 seconds. This pressure is a composition of the internal and external anal sphincter and, to a lesser extent, by the hemorrhoidal plexus.

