**Site 1 and 2 analysis**

The manometric parameters (maximum anal sphincter squeeze pressure (mmHg) and mean anal sphincter resting pressure (mmHg)) for the period before treatment would be compared against parameters after treatment. Clinical indicators Vaizey/Wexner faecal incontinence score, faecal incontinence episodes (days/week), frequency of bowel motions & symptoms, and patient’s own view of effectiveness rating will be analysed. Univariate analysis (paired t-test or Wilcoxon) will be used to evaluate manometric parameter changes, while chi square test will be used to compare clinical indicators.

Non-inferiority study analysis described in Section 5.3 will be used to determine if null hypothesis is accepted or rejected.

***
[figure not shown]
***

***Figure 3.*** *Summary of study procedure*

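### The tested non-inferiority margin is 0.44 of an unnamed SD, and it conflicts with the fixed losses that the same section accepts two sentences later

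*Protocol*

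**What the plan says.** Protocol section 5.3 (Site 2 sample size and power calculations) contains three statements that bear on the margin.

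- **The hypothesis.** The alternative is that "mean changes due to home-BF is no more than 0.44 SD lower than clinic-BF", set out formally as "Ho: ΔHB-ΔOB<−0.44SD vs. Ha: ΔHB-ΔOB≤−0.44SD". No SD is named, and both inequality signs point the same way, which looks like a misprint in the alternative. The claimed operating characteristic is that "the test for non-inferiority has 0.70 power to reject, at the 0.05 significance level", "with n=30 per study arm".
- **The criteria in native units.** The next paragraph says home-BF counts as no worse if it achieves "at least 9 point decrease in Vaizey/Wexner faecal incontinence score (11 for clinic-BF, SD=3"). It gives matching figures of 0.95 against 1.1 days/week (SD 0.25) for incontinence episodes and 19 against 25 mmHg (SD 10) for squeeze pressure.
- **The paired-test sentence.** Just before the hypothesis, a detectable change of 0.45 SD is equated with 8 points on the incontinence score and 0.6 in incontinence episodes.

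Under Site 1 and 2 analysis the verdict is sent back to this section: "Non-inferiority study analysis described in Section 5.3 will be used to determine if null hypothesis is accepted or rejected". Section 5.3 also says that Site 1 data will be used to improve the Site 2 analysis plan and its sample size calculation.

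**The concern.** A non-inferiority claim rules out a stated loss to the patient, so that loss has to be known before the data are seen. Here the only formal null hypothesis is in units of an SD that is not identified. The fixed figures that follow do not translate it, because they describe a larger loss. Two analysts could follow section 5.3 faithfully and test different margins.

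If one of them used the SD observed in Site 2, the tolerated loss would depend on how scattered the data turned out to be, and the error rate for any given number of points would not be controlled. Section 7.1 says the data will support a regulatory submission, so this ambiguity matters.

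**Working it through.** **Inputs, all from section 5.3:** margin 0.44 SD; 30 analysed per arm; significance level 0.05, sidedness not stated; SDs of 3 points, 0.25 days/week and 10 mmHg. Assumed here: true difference zero for power, and one-sided 0.05 unless noted.

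**1. The plan's power of 0.70.** The standard error of the difference is SD × sqrt(2/30) = 0.258 SD. Power = Φ(0.44/0.258 − 1.645) = Φ(1.704 − 1.645) = 0.52 (noncentral t, 58 df: 0.516). At one-sided 0.025 it is 0.40 (t: 0.39). So 0.70 is not reproduced. Reaching it at 0.44 SD takes 2 × (0.524 + 1.645)² / 0.44² = 48.6, i.e. 49 per arm, or 64 per arm at one-sided 0.025. Two unstated readings come close:

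- The 2-point margin at one-sided 0.025 gives 0.72 (t) or 0.73 (z).
- If SD means a single-visit SD and the before–after correlation is 0.7 (an assumption), the change has SD sqrt(2 × 0.3) = 0.775 of it, and power is 0.71.

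**2. The two sets of margins.**

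| Outcome | 0.44 × stated SD | Loss in next paragraph | That loss in SD | Power at that loss (t) |
|---|---|---|---|---|
| Incontinence score | 0.44 × 3 = 1.32 points | 11 − 9 = 2 points | 2/3 = 0.67 | 0.82 |
| Incontinence episodes | 0.44 × 0.25 = 0.11 days/week | 1.1 − 0.95 = 0.15 days/week | 0.15/0.25 = 0.60 | 0.74 |
| Squeeze pressure | 0.44 × 10 = 4.4 mmHg | 25 − 19 = 6 mmHg | 6/10 = 0.60 | 0.74 |

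No row agrees. At one-sided 0.025 the powers in the last column become 0.72, 0.63 and 0.63.

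**3. Which SD?** The paired-test sentence implies a score SD of 8/0.45 = 17.8, against the stated 3, and an episode SD of 0.6/0.45 = 1.33, against 0.25. On the score, 0.44 SD is therefore either 1.32 points or 0.44 × 17.8 = 7.8 points, the latter out of an expected clinic gain of 11.

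**4. If the observed SD s is used.** With observed difference d, the rule is (d + 0.44s)/(s × sqrt(2/30)) > 1.672. Since 0.44/0.258 = 1.704, this becomes d/(s × sqrt(2/30)) > −0.033. At a true loss of 1.32 points, the chance of passing is approximately Φ(0.033 − 1.32/(0.258 × SD)):

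| True SD of the score | Margin in points | Chance of declaring non-inferiority at a 1.32-point loss |
|---|---|---|
| 3 (stated) | 1.32 | 5% |
| 4.5 (assumed) | 2.0 | 14% |
| 6 (assumed) | 2.6 | 21% |
| 9 (assumed) | 4.0 | 30% |

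A fixed 1.32-point margin keeps this at 5% in every row. At one-sided 0.025 the scaled rule gives 2% at SD 3, 13% at SD 6 and 19% at SD 9, so the widening does not depend on sidedness.

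**The case against.** The strongest reply is that section 5.3 does state losses in native units, and that the analysis section refers to 5.3 as a whole. A reader might infer from the SD-based hypothesis that the protocol gives no native-unit loss. That is wrong. What stands against the reply is that the native-unit figures are not written as hypotheses, carry no significance level, may be thresholds for the home group's own mean rather than confidence-limit margins, and do not equal 0.44 SD.

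Secondly, nothing in the protocol says the margin will be rescaled by the trial's own SD. With the planning SDs it is fixed at 1.32 points, 0.11 days/week and 4.4 mmHg. This is a fair limit, and the inflated error rates are therefore conditional. The defect is that the text leaves both readings open.

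Thirdly, a reader might infer that scaling by the SD reduces the verdict to the sign of the observed difference. At one-sided 0.05 the cut-off is indeed close to zero (−0.008 SD), but that comes from 30 per arm against a margin of this size. A fixed 1.32-point margin at SD 3 gives −1.32 + 1.672 × 3 × 0.258 = about −0.025 points, which is the same cut-off. At one-sided 0.025 it moves to +0.077 SD. Under the 2-point margin (one-sided 0.05, SD 3) observed shortfalls up to 0.71 points pass. The documents do not support the sign result as a consequence of the scaling.

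Fourthly, an SD of 17.8, and the 40% false-claim rate it would produce, might be read as a realistic prospect. It is only evidence that two sentences of the section disagree.

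Finally, an analysis plan not shown here may name the SD. It could not satisfy both sets of figures while the protocol holds them side by side.

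**Conclusion.** The point holds in a limited form. The decision threshold for Site 2 is not fixed: the hypothesis names no SD, the section supports two very different score SDs, and the resulting margins (1.32 points, 0.11 days/week, 4.4 mmHg on the stated SDs) conflict with the losses accepted in the next paragraph (2 points, 0.15 days/week, 6 mmHg). The stated power of 0.70 follows from neither set at one-sided 0.05 with zero true difference and 30 per arm.

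The loss of error control, from about 5% at SD 3 to about 21% at SD 6, applies only if the observed SD defines the margin. SD 6 is an assumption, not a document figure. The conflict between the two sets of margins needs no such assumption.

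**What to change.** Before Site 2 opens, amend section 5.3 as follows:

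- Reconcile the 0.44 SD hypothesis with the native-unit criteria, and state in the hypotheses one fixed, justified margin per primary outcome in points, days/week or mmHg. Correct the inequality sign in the alternative.
- Test each margin with a confidence interval in raw units at a stated one-sided level, and say whether the 9-point, 0.95 days/week and 19 mmHg figures are margins or descriptive targets.
- State that the margins will not be rescaled from Site 1 or Site 2 data. Use the SD only for the power calculation, and correct the 0.45 SD conversions that imply a different SD.
- Restate the power for the margins chosen, using the figures above as a guide.

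The cost is wording and a recalculation. The downside is that power may look worse than 0.70, and it falls further if the real SD exceeds the planning value. With a fixed 2-point margin at one-sided 0.05, power drops from 0.82 at SD 3 to 0.45 at SD 5. With 1.32 points it drops from 0.52 at SD 3 to 0.21 at SD 6. Either could call for more participants.

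### Protocol Section 5.3 gives two non-inferiority criteria that disagree: a 0.44 SD between-arm margin, and home-arm targets that imply margins of 0.60 to 0.67 SD and, as worded, use no concurrent control

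*Protocol*

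**What the plan says.** Both criteria stand in Protocol Section 5.3, under the Site 2 sample size and power calculations.

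- **Between-arm test.** The null hypothesis is that the "mean change due to home-BF is smaller than clinic-BF by at least 0.44 SD". The alternative is that "mean changes due to home-BF is no more than 0.44 SD lower than clinic-BF". The calculation is made "with n=30 per study arm", and the protocol states that "the test for non-inferiority has 0.70 power to reject, at the 0.05 significance level".
- **Home-arm targets.** The next paragraph, using estimates from a previous study, says "we consider home-BF no worse than or better than clinic-BF if the home-BF group had at least 9 point decrease in Vaizey/Wexner". It gives the clinic change for that score as 11 with SD 3. For episodes the target is a fall of 0.95 days/week (clinic 1.1, SD 0.25). For the third outcome it is a "19 mmHg increase in anal sphincter squeeze pressure (25 mmHg for clinic-BF, SD=10").

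The design is a randomised parallel comparison: "Randomization used permuted blocks of 4 with 1:1 assignment into the parallel study groups" (Section 5.8). The Site 1 and 2 analysis in Section 5.8 says that the non-inferiority analysis of Section 5.3 will settle whether the null hypothesis is accepted or rejected. It does not say which of the two paragraphs it means.

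**The concern.** The two paragraphs differ in two ways.

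**Size.** The second paragraph looks like the first one put into raw units, but its figures do not equal 0.44 SD on the SDs printed beside them.

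**Comparator.** The first criterion compares two concurrent randomised arms at a stated significance level. The second, as worded, asks only whether the home group reaches fixed numbers. Its reference values come from an earlier study, and no confidence limit is involved.

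The two can therefore give opposite answers on the same data, in either direction. Non-inferiority of the home device is the trial's stated hypothesis (Section 3), and Section 7.1 says the data will be used in a regulatory submission. A plan that holds both criteria leaves room to choose between them once results are known.

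**Working it through.** **Inputs**, all from Section 5.3: margin 0.44 SD; 30 evaluable per arm; significance level 0.05 (sidedness not stated); stated power 0.70; clinic changes 11, 1.1 and 25; home targets 9, 0.95 and 19; SDs 3, 0.25 and 10. The symbols printed for the two hypotheses point the same way, so I take the direction from the sentence around them.

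**1. The protocol's own power figure.** For a two-sample test with true difference zero, power = Φ(margin/√(2/n) − z). With n = 30, √(2/30) = 0.258.
- One-sided 0.05: Φ(0.44/0.258 − 1.645) = Φ(0.059) = 0.52.
- One-sided 0.025: 0.40.

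The stated 0.70 is not reproduced. It would need a margin of 0.56 SD at one-sided 0.05, or 0.64 SD at one-sided 0.025.

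**2. Margins implied by the targets.** Implied margin = (clinic change − home target)/SD.

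| Outcome | Raw deficit allowed | In SD | 0.44 SD in raw units | Target that would match 0.44 SD |
|---|---|---|---|---|
| Incontinence score | 11 − 9 = 2 | 2/3 = 0.67 | 0.44 × 3 = 1.32 | 11 − 1.32 = 9.68 |
| Episodes (days/week) | 1.1 − 0.95 = 0.15 | 0.15/0.25 = 0.60 | 0.44 × 0.25 = 0.11 | 1.1 − 0.11 = 0.99 |
| Squeeze pressure (mmHg) | 25 − 19 = 6 | 6/10 = 0.60 | 0.44 × 10 = 4.4 | 25 − 4.4 = 20.6 |

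Ratios: 0.60/0.44 = 1.36 and 0.667/0.44 = 1.52, so the implied margins are 36% to 52% wider.

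**3. Opposite answers on the same data** (score, SD 3, 30 per arm, one-sided 0.05). The standard error of the difference is 3 × 0.258 = 0.775, so the lower bound lies 1.645 × 0.775 = 1.27 below the observed difference.
- Home 9, clinic 11: difference −2, bound −3.27. The test with margin 1.32 fails; the target of 9 is met.
- Home 8, clinic 8: difference 0, bound −1.27. The test passes; the target of 9 is missed.

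**4. Error rates if the targets were applied literally.** The home mean is taken as normal with standard error SD/√30. The clinic arm is assumed to sit at its historical values, with home truly 0.44 SD worse, which is the null boundary of the first test.
- Score: P(mean ≥ 9 given true 9.68, SE 0.548) = Φ(1.24) = 0.89.
- Episodes: P(mean ≥ 0.95 given true 0.99, SE 0.0456) = Φ(0.88) = 0.81.
- Squeeze: P(mean ≥ 19 given true 20.6, SE 1.826) = Φ(0.88) = 0.81.

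The between-arm test would pass each with probability 0.05. In the other direction, if both arms truly improve by 8 points, P(mean ≥ 9 given true 8, SE 0.548) = 1 − Φ(1.83) = 0.03, although the arms do not differ.

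**5. Power at 30 per arm, one-sided 0.05, by margin.** 0.44 SD: 0.52. 0.60 SD: Φ(0.60/0.258 − 1.645) = 0.75. 0.67 SD: Φ(0.667/0.258 − 1.645) = 0.83.

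**The case against.** **The between-arm test already decides.** Section 5.8 speaks of accepting or rejecting the null hypothesis, and only the between-arm test has one. The target paragraph sits under the power calculations, opens with estimates from a previous study and pairs each target with a clinic change and an SD. It may be no more than a translation of the margin into raw units for planning. This is a fair reading and weakens the point about the comparator. It does not remove it: Section 5.8 points to Section 5.3 as a whole, and the target paragraph is worded as a rule for when home treatment counts as no worse. On the milder reading, one margin still has two sizes.

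**SD may mean different things.** If 0.44 refers to the SD of a difference between two changes, it equals 0.44 × √2 = 0.62 of the SD of change, close to 0.60 and 0.67. The protocol does not say so, the score still does not match, and the power would be 0.78 (one-sided 0.05) or 0.67 (one-sided 0.025), again not 0.70. If 0.44 refers to the SD of single measurements with a before-after correlation of 0.7, power would be 0.71 at one-sided 0.05, but the protocol gives no such correlation. The 36% to 52% is therefore conditional on one meaning of SD. The comparator problem is not.

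**Stronger readings that the protocol does not support.**
- A reader might infer that the randomised control is discarded and that the trial's error rate is far above 0.05. That follows only if the targets are the deciding rule, and Section 5.8 leans the other way.
- A reader might multiply the three pass probabilities (0.89 × 0.81 × 0.81, about 0.59) and compare the result with 0.05. The product assumes independence between outcomes measured in the same patients. The 0.05 is stated for a single test, and the protocol gives no joint rate.
- A reader might conclude that 0.44 is a misprint for 0.60, because 0.60 SD with 27 per arm (40 less 33%) gives power 0.70. The protocol's calculation states 30 per arm, and at 30 a margin of 0.60 SD gives 0.75. The document does not show which figure is wrong.

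**Conclusion.** The point stands as an inconsistency in the decision criterion. On the SDs printed in Section 5.3, the between-arm margin and the raw-unit targets differ by 36% to 52%, provided that SD means the same in both paragraphs. The stated power of 0.70 does not settle which was intended: it fits neither 0.44 SD (0.52) nor 0.60 to 0.67 SD (0.75 to 0.83) at 30 per arm and one-sided 0.05.

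The second criterion, as worded, also omits the concurrent arm and any confidence bound. Section 5.8 suggests, without stating it, that this criterion is not the deciding one. The pass probabilities of 0.81 to 0.89 per outcome, and the 3% for two equally effective arms, show what would happen if it were applied literally. The former also assume that the clinic arm reproduces its historical values. They are not the error rates of the trial as it will necessarily be analysed.

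**What to change.** Before Site 2 starts:

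1. Fix one non-inferiority margin per primary outcome in raw units, justified by the sponsor on clinical grounds, and use it in both paragraphs of Section 5.3. Say which SD is meant wherever a margin is also given in SD units.
2. State that non-inferiority is declared only if the confidence bound for the randomised home-minus-clinic difference in improvement lies inside that margin, at the stated 0.05 level with its sidedness given. Make Section 5.8 refer to that rule.
3. Keep 9/11, 0.95/1.1 and 19/25 as planning values only, and say so.
4. Restate the power for the chosen margin with 30 per arm. At one-sided 0.05 it is about 0.52 at 0.44 SD, 0.75 at 0.60 SD and 0.83 at 0.67 SD.

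The cost is protocol wording, with no additional data collection. Section 5.3 already plans to revisit the Site 2 calculations with Site 1 data, so there is a natural occasion. The one possible further cost lies in the margin chosen: if 0.44 SD and 0.70 power were both kept, the two-sample calculation at one-sided 0.05 would need 49 evaluable per arm rather than 30.
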